## Methods

### Patient and public involvement

Participants or members of the public were not involved in the design, conduct, reporting, or dissemination plans of this research. The trial design and intervention protocols were developed by the research team based on previous studies conducted with similar older adult populations and on established recommendations for aquatic exercise programs. The acceptability and safety of the exercise sessions will be monitored throughout the intervention period, and participant feedback will be taken into consideration when interpreting the study findings.

### Trial design and setting

This trial is a randomized clinical trial employing a 1:1:1 allocation ratio. It was designed as a superiority trial with three parallel groups, and the outcome assessors and data analysis were blinded. This trial is being conducted at the School of Physical Education and Physiotherapy (ESEF) of the Federal University of Pelotas (UFPel), Brazil. The present study protocol was designed in accordance with the SPIRIT Statement 2025 [42].

### Eligibility criteria

The inclusion and exclusion criteria for participants are defined as follows:

#### Inclusion criteria

Older women aged 60 and 75 years;

Being physically inactive, meaning not participating in structured physical exercise for at least six months (regular exercise is defined as engaging in any physical training for a minimum of 20 min on two or more days a week).

#### Exclusion criteria

History of cardiovascular disease (except controlled hypertension);

Osteoarticular limitations for the practice of exercises;

Being illiterate due to the self-completion questionnaires and the characteristics of the intervention;

Diagnosis of dementia, schizophrenia, or major depressive disorder.

#### Rationale for sex-specific inclusion:

The study includes only older women to account for potential sex-related differences in aging trajectories relevant to the outcomes of interest, thereby reducing sex-related sample heterogeneity. In addition, aquatic exercise programs typically show greater participation among older women.

### Interventions and comparator

Participants will be randomized into one of three groups: an aquatic aerobic exercise program combined with cognitive tasks, a conventional aquatic aerobic exercise program, or a control group. Aquatic exercises will be standardized as exclusively aerobic due to their demonstrated effectiveness in improving physical function within the proposed 12-week period, as reported in previous studies [20, 21, 23–25]. Accordingly, both intervention groups will perform the same aquatic aerobic exercise program, while the group including cognitive tasks will receive this additional component, which is expected to account for potential differences between the groups. Participants allocated to the control group will not engage in any structured physical or cognitive interventions during the 12-week period. This design will allow us to determine whether any observed improvements in the intervention groups can be attributed to the exercise programs and their inherent characteristics, including the potential contribution of attention and social interaction effects associated with supervised group-based activities, rather than to external factors.

#### Aquatic exercise intervention groups

The intervention will take place at the thermal pool of Brilhante Club in Pelotas. The pool water temperature will be maintained between 30 and 32 °C, with participants immersed to a depth level between the xiphoid process and the shoulders. Participants in both exercise groups will undertake a 12-week exercise program, consisting of two weekly sessions on non-consecutive days. Each session will last 45 min, comprising a 5-min warm-up, 35 min of aerobic exercises, and a 5-min cool-down and stretching. The group with cognitive tasks will perform this additional component during the main part of the exercises. Both exercise groups will undergo one familiarization session with aquatic exercises and learn to use the Borg’s 6–20 rating of perceived exertion (RPE) scale before the start of the intervention. The exercise sessions will be conducted in groups of 8 to 12 participants and delivered by a physical education professional with a bachelor’s degree ([name]) and expertise in aquatic exercise prescription, under the supervision of the principal investigator ([name]). A second instructor will provide in-pool assistance throughout the sessions.

##### Conventional aquatic aerobic exercise program

The aquatic exercise sessions will include the following exercises: butt kick (Fig. 1A), frontal kick (Fig. 1B), cross-country skiing (Fig. 1C), and stationary running (Fig. 1D). These exercises are commonly used in aquatic exercise classes and provide controlled osteoarticular impact, being safe for older women [18].

**Fig. 1 Fig1:**
[figure not shown]
Aquatic exercises included in the sessions: **A** butt kick, **B** frontal kick, **C** cross-country skiing, and **D** stationary running

The program periodization is presented in Table 1. Training intensity will be controlled using the Borg 6–20 RPE scale [43]. The adopted strategy is based on interval training, which alternates periods of high-intensity effort with low-intensity active recovery. Each block will consist of 4 min of effort, with one minute for each exercise (butt kick, frontal kick, cross-country skiing, and stationary running), followed by 1 min of active recovery, also performed using the stationary running exercise. To facilitate monitoring, an RPE scale (0.90 × 1.20 m) will be positioned outside the pool, in front of the participants.

**Table 1 Tab1:** Periodization of the 12-week aquatic aerobic exercise program

Weeks	Sets	Exercises	Duration	Intensity	Total Duration
1–4	7	Butt Kick	4 min	RPE 13	35 min
		Frontal Kick			
		Cross-Country Skiing			
		Stationary Running			
		Stationary Running	1 min	RPE ≤ 11	
5–8	7	Butt Kick	4 min	RPE 14	35 min
		Frontal Kick			
		Cross-Country Skiing			
		Stationary Running			
		Stationary Running	1 min	RPE ≤ 11	
9–12	7	Butt Kick	4 min	RPE 15	35 min
		Frontal Kick			
		Cross-Country Skiing			
		Stationary Running			
		Stationary Running	1 min	RPE ≤ 11	

*RPE* rating of perceived exertion

##### Aquatic aerobic exercise program combined with cognitive tasks

This group will perform the same aerobic exercise program as the conventional group. Additionally, cognitive tasks will be included during each 1-min active recovery, for a total of 7 min per session. Cognitive training will encompass different domains of cognition in all sessions, including processing speed, attention, inhibitory control, memory, cognitive flexibility, and semantic fluency. The program's targeted cognitive domains were selected for their recognized importance for cognitive health in later life. The selected cognitive tasks are closely related to executive functions, which are essential for everyday functioning. The structure of cognitive training is detailed in Table 2.

**Table 2 Tab2:** Description of the cognitive tasks used in the program

Domain	Cognitive task	Duration
Processing speed	Listen to the command and execute it as quickly as possible (e.g., touch your head, shoulders, hips, and knees)	1 min
Attention	Count the number of times a previously chosen number is mentioned in a spoken sequence	1 min
Inhibitory control	Perform the opposite command to the statement (e.g., wave your hands only when a specific word is said, and do not react to the others	1 min
Memory	Execute the command previously associated with the color of the plate shown (e.g., red plate – alternating push forward; green plate – elbow flexion and extension)	1 min
Cognitive flexibility	Say a word related to the previous word (e.g., car—tire—rubber—pencil)	1 min
Memory and attention	Repeat the word said previously and add a new one in sequence (e.g., blue; blue and pink; blue, pink, and green…)	1 min
Semantic fluency	In pairs, one-participant names as many words related to a specific topic (e.g., cities, colors, or fruits) as possible in 30 s, while the other counts; afterward, the roles are switched between participants	1 min
Total volume/session		7 min

These domains support daily activities such as quickly evaluating the distance and speed of vehicles when crossing the street (processing speed); maintaining focus while performing domestic tasks without becoming distracted (attention); resisting the urge to stand up abruptly when hearing the phone ring, thereby reducing the risk of falls (inhibitory control); remembering to take medications at the correct times or recalling recently received instructions (memory); adapting to unexpected changes in daily routines, such as modifying a planned route or strategy when circumstances change (cognitive flexibility); and naming objects, foods, or places efficiently during conversations, thereby facilitating communication and reducing pauses or word-finding difficulties (semantic fluency).

The cognitive tasks incorporated into the intervention were designed to increase cognitive load by engaging multiple cognitive domains during simultaneous motor execution, thereby simulating real-world dual task demands. To ensure continuous stimulation and reduce adaptation, task commands varied across sessions, and new commands targeting all cognitive domains were introduced within each mesocycle. Although the intervention did not include a formally structured progression of cognitive load or task complexity across mesocycles, this variability was intended to progressively challenge participants. Furthermore, the cognitive tasks were developed to engage the targeted domains during exercise while avoiding direct overlap with outcome-assessment tasks, thereby minimizing potential learning effects and preserving the validity of the cognitive outcome measures.

#### Control group

The control group will be instructed to maintain their usual physical activity habits and cognitive routines.

#### Criteria for discontinuing or modifying allocated interventions

Participants may discontinue the study at any time if they lose interest or are no longer willing to continue. Participation will be interrupted for individuals allocated to any group in case of safety concerns, such as medical advice or a health event that precludes attendance at intervention sessions.

#### Strategies to improve adherence to interventions

The aquatic exercise intervention groups will receive messages at the beginning of each week, reinforcing the date, time, and location of the sessions. A member of the research team will make phone calls or WhatsApp messages to inquire about adverse events if a participant misses a session in any of the intervention groups. The call schedule will be discontinued for participants who withdraw from the study. Participants assigned to the control group will be informed upon allocation that they will receive the aquatic exercise program after completing their participation in the study.

#### Concomitant care permitted or prohibited during the trial

Participants will be instructed not to engage in any other activities involving exercise or cognitive training during the study period. Participants are also advised to maintain their regular eating habits and continue their treatment for any existing illnesses.

### Outcomes

The primary outcome of the study is executive function (verbal fluency subtype), assessed by the Controlled Oral Word Association Test (COWAT; total F-A-S score), which captures aspects of inhibitory control, cognitive flexibility, and verbal initiation. The primary endpoint is the post-intervention time point. The primary analysis will focus on between-group differences at post-intervention, with additional longitudinal analyses examining changes from baseline and the maintenance of effects at follow-up (12 weeks after the end of the intervention).

The secondary outcomes of the study will be presented as group means and include:

Cognitive function, which will be assessed at baseline, post-intervention, and at the 12-week follow-up after the end of the intervention time points:Attention span and short-term memory, measured by the Digit Span Test – Forward (DST–F);Processing speed and visual attention, measured by the Trail Making Test – part A (TMT–A);Executive function (set-shifting ability), measured by the Trail Making Test – part B (TMT–B);Self-perceived cognitive failures, measured by the Cognitive Failures Questionnaire (CFQ).

Physical Function, which will be assessed at baseline and post-intervention time points:Aerobic fitness, measured by the 6-min Walk Test (6MWT);Lower limb strength, measured by performance in the 30-s Chair Stand Test;Upper limb strength, measured by performance in the Arm Curl Test;Lower limb flexibility, measured by the Sit-and-Reach Test (Wells Bench);Agility and dynamic balance, measured by performance in the Timed Up and Go (TUG) Test;Dual-task performance, measured using the TUG combined with a simultaneous cognitive task.

Cardiovascular parameters, which will be assessed at baseline and post-intervention time points:Office blood pressure, measured using a calibrated and automated oscillometric device;Heart rate variability, measured using a heart rate monitor;Blood pressure reactivity, measured using the auscultatory method during the Stroop Test for 3 min;Heart rate reactivity, measured using a heart rate monitor during the Stroop Test for 3 min.

Psychosocial parameters, which will be assessed at baseline and post-intervention time points:Depressive and anxiety symptoms, measured by the Hospital Anxiety and Depression Scale (HADS);Sleep quality, measured by the Pittsburgh Sleep Quality Index (PSQI);Quality of life, measured by the World Health Organization Quality of Life—BREF (WHOQOL-BREF) questionnaire.

### Harms

Adverse events will be systematically collected at the end of every week and classified based on their severity (i.e., mild, moderate, or severe), predictability (i.e., expected or unexpected), and potential relationship to study procedures (i.e., definitely related, possibly related, or unrelated). All adverse events are reviewed by a multidisciplinary team that includes at least two clinical experts ([name], [name], TR, [name]).

### Participant timeline

The trial enrollment, interventions, and assessments schedule is presented in Table 3.

**Table 3 Tab3:** Time scheme for the study conduction

	Study period								
	Enrollment	Baseline measures		Allocation	Post-allocation		Close out		
	T −1	T0^a^		T1	T2	T3^b^	T4^a^		T5
Time point description		Evaluation visit 1	Evaluation visit 2		Intervention start	Intervention End	Final evaluation visit 1	Final evaluation visit 2	Follow-up
Enrollment									
Eligibility screening	X								
Informed consent	X								
Allocation				X					
Interventions									
Aquatic aerobic exercise program combined with cognitive tasks					X	X			
Conventional aquatic aerobic exercise program					X	X			
Control group					X	X			
Assessments									
*Primary outcome*									
Objective cognitive function by COWAT			X					X	X
*Secondary outcomes*									
Objective cognitive function by DST–F			X					X	X
Objective cognitive function by TMT–A/B			X					X	X
Self-perceived cognitive function		X					X		X
Functional tests			X					X	
Heart rate variability			X					X	
Office blood pressure		X	X				X	X	
Blood pressure and heart rate reactivity			X					X	
Depressive and anxiety symptoms		X					X		
Sleep quality		X					X		
Quality of life		X					X		
*Other outcomes*									
Cognitive status		X					X		
Sociodemographic and clinical characteristics		X					X		
Anthropometric measurements			X					X	
Physical activity levels		X					X		
Eating habits		X					X		
Monitoring the intensity of training sessions					X	X			
Adherence assessments					X	X			
Satisfaction questionnaire								X	

*COWAT* Controlled Oral Word Association Test, *DST–F* Digit Span Test – Forward, *TMT* Trail Making Test

^a^period will be no longer than 2 weeks

^b^time between t3 and t4 will be no longer than 2 weeks

### Sample size

The sample size was calculated using G*Power 3.1 software, based on the study’s primary outcome, assessed by the COWAT, using unpublished data from our laboratory. An effect size of ƒ = 0.180 was used, with 90% power and an alpha of 5%. The calculation indicated a required sample of 84 participants, with an additional 20% added to account for potential dropouts, resulting in 102 participants to be recruited.

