### Statistical methods

Descriptive data will be presented as means with standard deviations and/or 95% confidence intervals, or as absolute or relative frequencies, when applicable. Generalized Estimating Equations (GEE) will be used to compare primary and secondary outcomes, assuming an unstructured working correlation matrix. In all GEE models, group and time will be treated as categorical variables, and group × time interactions will be included to test intervention effects. Bonferroni-adjusted post hoc tests will be applied when multiple comparisons are performed. The efficacy of the trial will be assessed using a single pre-specified primary outcome and a single primary comparison, consistent with SPIRIT recommendations for clinical trial protocols. Therefore, no multiplicity adjustment across outcomes will be applied. Analyses of secondary outcomes will be considered exploratory, and multiplicity adjustments will be applied only for multiple comparisons within the same outcome (e.g., Bonferroni-adjusted post hoc tests).

Both per-protocol (PP) and intention-to-treat (ITT) analyses will be conducted. In the analysis following the ITT principle, all randomized participants are analyzed in the group to which they were initially assigned, regardless of adherence, treatment receipt, or protocol deviations. Multiple imputations will be used to impute missing data using a specific function on SPSS software. Additionally, PP analyses will be performed to evaluate the robustness of the findings and the effect of adherence to the intervention. Therefore, participants must have at least 70% attendance during the 12-week intervention to be included in the PP analysis. This threshold was defined to ensure sufficient exposure to the training stimulus to plausibly induce adaptations, while accounting for the variability in attendance commonly observed in exercise interventions involving older adults. This cutoff has been adopted in previous aquatic exercise intervention studies conducted by our research group involving older populations under similar conditions [22].

No additional analyses, such as subgroup or sensitivity analyses, are planned for this trial. All statistical procedures will be performed in the SPSS vs. 28.0 program, and the significance level adopted is α = 0.05. Additionally, between-group effect sizes will be calculated using Cohen's d based on change scores and classified as small (≥ 0.2), moderate (≥ 0.5), or large (≥ 0.8) [60, 61].

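### The 90% power with 84 women comes from a repeated-measures calculation and is not shown for the declared primary analysis, a single unnamed between-group comparison at post-intervention

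*Protocol article*

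**What the plan says.** Under Sample size, the protocol article uses G*Power 3.1 with an effect size of f = 0.180 for COWAT, obtained "using unpublished data from our laboratory". That effect size "was used, with 90% power and an alpha of 5%. The calculation indicated a required sample of 84 participants". A 20% allowance for dropout then brings recruitment to 102. The section does not give the G*Power test, the number of measurements, the correlation between them, or whether f is a between-group effect at one visit or an interaction effect.

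Under Outcomes, post-intervention is the primary endpoint and "The primary analysis will focus on between-group differences at post-intervention". Statistical methods says that efficacy rests on "a single pre-specified primary outcome and a single primary comparison" but does not say which two groups are compared. The same section specifies GEE models in which the group by time interaction tests intervention effects. Allocation is 1:1:1, so 84 is 28 per arm and 102 is 34 per arm.

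**The concern.** A power statement should belong to the test that decides the trial. Here that test is one contrast between two arms at one visit, while the sample size behaves like that of a repeated-measures effect across several visits. In a 3 x 3 layout the interaction has 4 degrees of freedom. It draws on differences from control and on the follow-up visit as well as on the post-intervention contrast, so its power does not carry over to one pair at post-intervention.

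The Background says that what has not yet been proven is whether cognitive tasks add to the same aquatic programme. If the single primary comparison is combined versus conventional exercise, a null result would be read as coming from a trial with 90% power, when its power could be about half that.

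**Working it through.** **Inputs.** From the protocol article: f = 0.180, alpha 0.05, power 0.90, N = 84 (28 per arm), 102 recruited (34 per arm), three groups, COWAT measured three times. Assumed, because not stated: correlation between measurements (0.5 unless noted), no nonsphericity correction, two-sided pairwise tests.

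**Step 1: reproduce 84.** For the repeated-measures interaction with k groups, m measurements and correlation r, the noncentrality is λ = f²·N·m/(1 − r), with df (k − 1)(m − 1) and (N − k)(m − 1).

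- 3 groups x 3 times, r = 0.5, N = 82: λ = 0.0324 x 82 x 3/0.5 = 15.94, df 4 and 158, power 0.901. At N = 84, λ = 16.33 and power is 0.909. So 82 are needed, or 84 in equal arms.
- 3 x 2, r = 0.6, N = 84: λ = 0.0324 x 84 x 2/0.4 = 13.61, power 0.910 (82 needed, 84 in equal arms).
- Time effect, 3 groups, 2 measurements, r = 0.5, N = 84: λ = 10.89, power 0.903.
- Interaction, 2 groups x 2 times, r = 0.5, N = 84: λ = 10.89, power 0.903. This is a one-degree-of-freedom test, but it has 42 per arm and the trial has 28.

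All four are repeated-measures settings. Calculations of a between-group effect with the same f do not give 84:

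- One-way test at post-intervention (λ = f²·N): 394, or 396 in equal arms.
- Repeated-measures between-group effect, 3 times, r = 0.5: 264.
- Baseline-adjusted three-group test (λ = f²·N/(1 − r²)): 296 at r = 0.5 and 203 at r = 0.7. It reaches 84 only if r is just under 0.9.

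**Step 2: what f = 0.18 implies for one pair.** Take f as the interaction effect, in line with how 84 reproduces. Then f = SD(group pattern) x SD(time pattern). The time SD is 0.5 for two visits (0, 1), √(2/9) = 0.471 for three visits with the effect maintained (0, 1, 1), and √(1/6) = 0.408 if half is kept (0, 1, ½). The group SD is therefore 0.18/0.5 = 0.360, 0.18/0.471 = 0.382 or 0.18/0.408 = 0.441.

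- Equally spaced arms (combined > conventional > control): neighbouring arms differ by 1.225 group SDs, which is 0.44, 0.47 or 0.54 SD of COWAT. The outer pair differ by twice that, 0.88 to 1.08 SD.
- One arm apart from two equal arms: the difference is 2.121 group SDs, 0.76 to 0.94 SD.

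**Step 3: power for one pair.** Noncentral t with 2n − 2 df and noncentrality d·√(n/2). For baseline adjustment, d is divided by √(1 − r²).

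| Contrast | d (SD) | 28 per arm, unadjusted | 28 per arm, adjusted r = 0.5 | 34 per arm, unadjusted | 34 per arm, adjusted r = 0.5 |
|---|---|---|---|---|---|
| Combined vs conventional, equal spacing | 0.44-0.54 | 37-51% | 46-63% | 43-59% | 54-72% |
| Combined vs control, equal spacing | 0.88-1.08 | 90-98% | 96-99.6% | 95-99% | 98% or more |
| Pair that includes an arm standing apart | 0.76-0.94 | 80-93% | 90-98% | 87-97% | 95-99% |

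For combined versus conventional at 28 per arm, adjustment with r = 0.7 gives 62-79%. A change-score comparison with r = 0.5 gives the unadjusted figures, because its variance is 2(1 − 0.5)σ² = σ².

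**Step 4: detectable difference at 90% power.** At 28 per arm: 0.88 SD unadjusted, 0.76 SD adjusted at r = 0.5, 0.63 SD at r = 0.7. At 34 per arm: 0.80, 0.69 and 0.57 SD.

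**The case against.** The best defence is that the calculation fits the planned model. Statistical methods tests intervention effects through the group by time interaction in a GEE over the COWAT visits, and a 3 x 3 interaction at correlation 0.5 gives the stated figure. That stands: the arithmetic is sound and the calculation is related to the plan. But the same section, together with Outcomes, declares a narrower primary test, and the 90% does not transfer to it.

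A second defence is that the primary pair may be combined versus control, which is also among the stated hypotheses. Under the graded pattern that pair has about 90% power or more at 28 per arm. This stands too, and it is why the conclusion must be conditional on the pair.

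It could also be said that an article leaves such detail to a fuller document. That is weak here, because the Open science section says the whole protocol, including the statistical analysis plan, is in the article.

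A reader might infer more than the document supports:

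- **That the trial has 28.5% power and needs 396 women.** Those are the one-way figures when f = 0.18 is a between-group effect at post-intervention. The article does not define f that way, and that reading would not have produced 84.
- **That a Bonferroni correction lowers the power further.** The article applies it when several comparisons are made. A single primary comparison needs none.
- **That 84 arises only from omnibus tests.** The two-group, two-time interaction has one degree of freedom and also gives 84, although with 42 per arm.

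**Conclusion.** The point holds in conditional form. The 84 women and 90% power match repeated-measures settings and are not shown for the single post-intervention comparison declared as primary. The document does not establish that the trial is underpowered for its primary question, because it names neither the pair nor the meaning of f.

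The exposure is largest for combined versus conventional exercise: about 37-51% unadjusted or 46-63% baseline-adjusted at 28 per arm, and 43-59% or 54-72% if all 34 per arm contribute. These figures assume that f is the interaction effect, that the arms are equally spaced and, for the adjusted values, a baseline-post correlation of 0.5. A higher correlation improves them (62-79% at 0.7 with 28 per arm) but does not bring them to 90%. If the primary pair is combined versus control, or includes an arm that stands apart from the other two, unadjusted power at 28 per arm is about 80-98%.

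**What to change.** Keep 102 women and rewrite the Sample size paragraph:

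- Name the single primary contrast in Statistical methods and repeat it in Sample size, for example combined minus conventional, COWAT total, post-intervention, two-sided 5%, baseline-adjusted.
- State the G*Power test, the number of measurements, the correlation and the meaning of f behind the 84, and say that the 90% refers to that repeated-measures test.
- Give the COWAT SD and baseline-post correlation from the laboratory data, and report power or the detectable difference for the named contrast at 28 and 34 per arm.

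The cost is a reworded paragraph and one named contrast, with no extra participants. Recruitment is expected to run until August 2027, so this can be done before analysis. The drawback is that the stated power may become less favourable.
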